## Abstract

**Background:** Chronic non-communicable diseases—chiefly chronic obstructive pulmonary disease (COPD), type 2 diabetes mellitus (T2DM), and cardiovascular diseases (CVDs)—remain the leading causes of morbidity and mortality worldwide. Despite the proliferation of telehealth programs, few longitudinal studies have rigorously evaluated theory-based, nurse-led digital education across multiple chronic conditions within a unified self-care framework. PROSELF (Promotion of Self-Care through Educational Interventions in Chronic Patients) addresses this gap. **Methods:** Promotion of Self-Care (PROSELF) is a prospective, longitudinal, multicenter, non-interventional study in community and primary-care settings in Southern Italy. A 12-month nurse-led digital educational intervention—grounded in the Middle-Range Theory of Self-Care of Chronic Illness—targets the three core self-care dimensions (maintenance, monitoring, and management) through individualized tele-education, asynchronous reinforcement, and structured follow-up at baseline, 3, 6, and 12 months. Validated self-care, quality-of-life, and social-support measures will be used. Data will be analyzed using repeated-measures and multivariate models to evaluate longitudinal changes in self-care, adherence, and related outcomes. Participation requires digitally informed consent. **Results:** The PROSELF study is expected to demonstrate the effectiveness of a 12-month, nurse-led digital educational program in improving adherence and self-care behaviors among patients with chronic diseases (COPD, diabetes, and cardiovascular disease). The intervention will leverage validated self-care assessment tools and tele-educational follow-up sessions. **Conclusions:** Findings from this study will inform the design of scalable, evidence-based, behaviorally informed models for digital chronic care delivery and nursing education.

## 1. Introduction

Chronic diseases account for approximately 41 million deaths annually and more than 70% of healthcare expenditure globally, placing sustained pressure on health systems and communities [1]. Pulmonary disease (COPD), type 2 diabetes mellitus (T2DM), and cardiovascular diseases (CVDs) share a long-term course, high risk of exacerbations, and a strong dependence on daily behaviors—adherence to therapy, self-monitoring, and timely help-seeking that cannot be achieved by clinical encounters alone [2,3,4]. In this landscape, self-care has emerged as a cornerstone of person-centered chronic care.

The growing burden of chronic diseases has exposed critical weaknesses in traditional healthcare models, which often rely on episodic, hospital-centered care and fail to address patients’ long-term behavioral needs. In this context, the integration of digital health technologies and nurse-led educational interventions has emerged as a promising approach to improve self-management and continuity of care. However, despite the growing availability of digital tools, structured and theory-based educational models led by nurses remain scarce, particularly in community and primary care settings.

The necessity of the Promotion of Self-Care through Educational Interventions in Chronic Patients (PROSELF) protocol arises from this gap. It aims to operationalize the goals of the Italian National Recovery and Resilience Plan (PNRR—Mission 6 “Health”), which emphasizes proximity care, patient empowerment, and the strategic role of Family and Community Nurses (FCNs) in digitally supported chronic disease management. By designing and evaluating a 12-month, nurse-led digital educational program grounded in the Middle-Range Theory of Self-Care of Chronic Illness, PROSELF seeks to provide a reproducible framework that strengthens evidence-based practice and informs future policy development in community health nursing.

The Middle-Range Theory of Self-Care of Chronic Illness defines self-care as a cyclical, adaptive process comprising maintenance (health-promoting and adherence behaviors), monitoring (recognition/interpretation of signs and symptoms), and management (appropriate responses and decision-making in collaboration with professionals) [5]. Yet, despite decades of initiatives, adherence and self-management remain suboptimal due to low health literacy, variable digital competence, and fragmentation across care pathways [6,7,8].

The COVID-19 pandemic accelerated the adoption of telehealth and digital education, revealing their potential to sustain continuity of care and support behavioral change at scale [9,10]. International experiences—particularly in the UK and Scandinavian countries—show that community nurses can effectively lead digital self-management programs, improving patient engagement and outcomes [11,12]. In Italy, the Piano Nazionale di Ripresa e Resilienza (PNRR)—Missione 6 “Salute” places the Family and Community Nurse (FCN) at the center of territorial, digitally supported chronic care. However, robust longitudinal evaluations of theory-driven, nurse-led digital education within this new framework are lacking [13,14].

PROSELF is designed to fill this gap. The intervention is explicitly theory-based [5], complemented by behavioral frameworks—Bandura’s Self-Efficacy and the Health Belief Model—to strengthen motivational components and perceived benefits/barriers [5,15,16].

Both theoretical frameworks were selected for their complementary relevance to behavioral change in chronic disease self-management. Bandura’s Self-Efficacy Theory emphasizes that individuals’ belief in their capability to execute specific behaviors directly influences persistence, motivation, and long-term adherence—constructs particularly relevant to medication routines, symptom monitoring, and help-seeking behaviors. The Health Belief Model (HBM), on the other hand, explains how perceived risk, benefits, and barriers influence health decisions and engagement in preventive actions. Within the PROSELF framework, self-efficacy components such as mastery experience, feedback, and goal setting are applied uniformly across conditions, whereas HBM-related constructs (perceived severity, susceptibility, and cues to action) are emphasized mainly for cardiovascular and metabolic diseases, where risk perception has a stronger motivational value. This integration ensures that the intervention remains both theoretically grounded and adaptable to disease-specific behavioral determinants.

The study evaluates 12-month effects on global and domain-specific self-care and on secondary outcomes (adherence proxies, health-related quality of life, perceived social support), while identifying predictors of improvement.

The primary objective is to quantify changes in overall self-care at 12 months.

Secondary objectives are (i) to assess changes across maintenance, monitoring, and management domains; (ii) to evaluate the effects of nurse-led digital education on treatment adherence, health-related quality of life, and perceived social support; and (iii) to identify predictors of improvement and patient engagement during follow-up.

Research hypotheses are integrated with these objectives. Specifically, we hypothesize that

(1)Participation in the PROSELF program will significantly improve self-care maintenance, monitoring, and management behaviors over time (linked to the primary objective i);(2)Nurse-led digital educational interventions will enhance adherence and perceived self-efficacy (linked to secondary objective ii);(3)Improvements in self-care and adherence will be associated with a higher quality of life and stronger perceived social support at 12 months (linked to secondary objective iii).

These hypotheses will be tested using validated self-care, quality-of-life, and social-support measures, as detailed in Section 2.

## 2. Materials and Methods

### 2.1. Study Design

PROSELF is a prospective, longitudinal, multicenter, non-interventional protocol with four assessments: baseline (T0), 3 months (T1), 6 months (T2), and 12 months (T3). The design follows SPIRIT 2013 for protocol transparency and STROBE recommendations for observational studies [17,18]. The study aligns with the organizational and digital priorities of Italy’s National Recovery and Resilience Plan Mission 6—health.

### 2.2. Setting and Participants

The study will be conducted in community and primary-care services across Southern Italy, including FCN clinics, general practice networks, and chronic disease outpatient pathways. Inclusion: adults (≥18 years) with a confirmed diagnosis of COPD, T2DM, or CVD; clinically stable at enrollment; access to internet-enabled devices; ability to consent and participate in tele-education. Exclusion: cognitive or psychiatric conditions precluding participation—such as moderate to severe dementia, major depressive disorder with psychotic features, schizophrenia spectrum disorders, or acute manic or psychotic episodes—severe uncorrected sensory impairments, or concurrent enrollment in interventional trials. Participants will be referred by FCNs and General Practitioners (GPs) during routine care or teleconsultation. Additionally, participants who already demonstrate optimal or near-optimal self-care behaviors—such as consistent treatment adherence, regular symptom monitoring, and proactive disease management—will be excluded based on baseline screening, to ensure measurable intervention effects. Eligibility will be verified using data from participants’ electronic medical records, reviewed and confirmed by the referring Family and Community Nurses (FCNs) or General Practitioners (GPs). Only objectively documented diagnoses (COPD, T2DM, or CVD) and clinical stability will be considered valid for inclusion. Self-reported data will be limited to sociodemographic and behavioral variables such as education, smoking habits, and physical activity.

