### 2.7. Outcomes

**Primary outcome**. Change in SC-CII total (0–100) from T0 to T3 (12 months), with domain-specific analyses (maintenance, monitoring, and management). An ≥8-point increase is treated as clinically important.

**Secondary outcomes**. Change in disease-specific self-care (SCHFI/SCODI/SCCOPD), HRQoL (EQ-5D-5L index and VAS; SF-36 PCS/MCS), perceived social support (MSPSS), and engagement/satisfaction with the digital education (brief evaluation form anchored to established telehealth assessment domains).

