### 2.11. Ethical Considerations

The study adheres to the Declaration of Helsinki (2013) and the ICN Code of Ethics for Nurses (2021) and complies with EU GDPR (2016/679) [32,33,34]. At manuscript submission, ethics approval is pending at the Campania 2 Ethics Committee. No recruitment or data collection will start before approval is granted. All participants will provide digital informed consent via secure authentication, with explicit statements on voluntariness, withdrawal, confidentiality, and data handling.

Participants may withdraw from the study at any time without consequences for their ongoing care. Interventions may be discontinued or rescheduled in case of significant worsening of the clinical condition, hospitalization, or explicit request from the patient. Concomitant care (e.g., pharmacological therapy, physiotherapy, and nutritional counseling) will continue as usual and will not be restricted by the study protocol. No additional or experimental interventions will be introduced during participation.

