### Strengths and Limitations

A central strength of PROSELF is its theory-driven design: the intervention content, the primary outcome (SC-CII), and the analysis plan are aligned with the three domains of self-care, ensuring conceptual integrity and interpretability. The 12-month follow-up allows assessment of behavioral consolidation—often missing in shorter digital education trials. The protocol emphasizes fidelity (standardized training, session audits), data integrity (automated checks, audit trail), and methodological transparency (SPIRIT/STROBE), enhancing reproducibility. Limitations include the non-randomized sampling and reliance on self-reported measures, which may introduce selection and response biases. These risks are mitigated by standardized administration, validated instruments, sensitivity analyses, and subgroup exploration (e.g., by digital literacy). While adverse events are not expected, we remain vigilant to potential discomfort during telecommunication and provide technical support. The absence of a control group limits causal inference; however, the longitudinal design, domain-specific outcomes, and multivariate modeling support credible real-world evidence. Future research should consider multicenter randomized designs and cost-effectiveness analyses.

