## Figures and Tables

**Table 1 healthcare-13-02972-t001:** SWOT analysis of the PROSELF protocol from patient and nurse perspectives.

Domain	Strengths	Weaknesses	Opportunities	Threats
Patient’s perspective	Personalized, theory-based tele-education addressing self-care behaviors. Accessible digital format, reducing geographical barriers. Integration of validated instruments (SC-CII, SCHFI, SCODI, and SCCOPD).	Digital literacy variability may limit engagement. Possible attrition over the 12-month follow-up.	Empowerment through continuous feedback and digital literacy. Potential scalability in community-based chronic care programs.	Risk of low adherence to scheduled video sessions. Potential connectivity issues in rural areas.
Nurse’s perspective	Standardized training ensuring intervention fidelity. Clear theoretical foundation (Riegel’s self-care theory).	Increased workload for FCNs/APNs in initial phase. Need for ongoing supervision.	Strengthening of advanced nursing role within PNRR Mission 6. Creation of a replicable tele-education model.	Institutional and logistical barriers to digital infrastructure adoption.

**Table 2 healthcare-13-02972-t002:** Participant progress, intervention program, and data collection timeline.

Timepoint	Key Activities	Instruments Administered	Outcomes Assessed
T0 (Baseline)	Eligibility screening; informed consent; first tele-education session	SC-CII; disease-specific scale; EQ-5D-5L; SF-36; MSPSS	Baseline self-care, HRQoL, support scores
T1 (3 months)	Second tele-education session; reinforcement materials	SC-CII; disease-specific scale; MSPSS	Interim change in self-care and support
T2 (6 months)	Third session; adherence monitoring review	All instruments	Mid-term improvement and engagement
T3 (12 months)	Final session; overall evaluation	All instruments	Long-term self-care and HRQoL outcomes

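### The self-care exclusion is not kept separate from the T0 score, so regression to the mean can enter the uncontrolled T0–T3 endpoint, while the abstract speaks of demonstrating effectiveness

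*Protocol article*

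**What the plan says.** **Selection.** Section 2.2 removes "participants who already demonstrate optimal or near-optimal self-care behaviors", giving treatment adherence, symptom monitoring and disease management as examples. They "will be excluded based on baseline screening, to ensure measurable intervention effects". No instrument or threshold is given. The same section says that eligibility is verified from electronic medical records by the referring nurse or GP.

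**Timing.** The T0 row of Table 2 lists "Eligibility screening; informed consent; first tele-education session" and, in the same row, the SC-CII and the other baseline instruments.

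**Endpoint and test.** Section 2.7 defines the primary outcome as the change in SC-CII total from T0 to T3, with 8 points or more treated as clinically important. Section 2.8 tests change over time within subjects, with Bonferroni-adjusted timepoint contrasts after a significant omnibus test.

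**Conclusions.** The Abstract says the study "is expected to demonstrate the effectiveness of a 12-month, nurse-led digital educational program". Strengths and Limitations says: "The absence of a control group limits causal inference; however, the longitudinal design, domain-specific outcomes, and multivariate modeling support credible real-world evidence". It also mentions selection and response bias, but not regression to the mean.

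**Label.** Section 2.1 states: "PROSELF is a prospective, longitudinal, multicenter, non-interventional protocol with four assessments". Section 2.11 adds: "No additional or experimental interventions will be introduced during participation". Sections 2.5 and 2.14 describe four tele-education sessions over 12 months, with material in between, for every participant.

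**The concern.** The three behaviours used as examples for the exclusion correspond to what the SC-CII measures. If people are kept because they look low on that construct at T0, some of them are low only through measurement error or a passing bad spell. Their later scores drift up without any intervention. With no control group, the T0–T3 change cannot separate that drift from a programme effect, and the drift always points in the programme's favour.

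The stated reason for the exclusion, to secure a measurable effect, makes this more than a detail of recruitment. The mitigations listed in the article (standardised administration, validated instruments, sensitivity and subgroup analyses, multivariate modelling) do not remove it. At stake are the meaning of a significant primary test, some inflation of the estimated gain, and whether effectiveness can be concluded at all.

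**Working it through.** The article gives no figure for this bias, so there is none to reproduce. The check asks how large it could be with zero programme effect.

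**Inputs from the article**
- Correlation among repeated measures r = 0.50 (Section 2.3).
- SC-CII test–retest ICC of at least 0.75 (Section 2.6), used as the higher value of r.
- N = 180 with 15% attrition (Section 2.3): 180 × 0.85 = 153 completers.
- Four timepoints, hence 4 × 3 / 2 = 6 pairwise contrasts if all are tested: two-sided level 0.05/6 = 0.0083.

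**Assumptions not in the article**
- Scores are bivariate normal with SD 15–20 points.
- The screen removes the top share q of T0 scores, with q = 10%, 25% or 40%.

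**Formulas** (SD units; c is the 1−q normal quantile; λ = φ(c)/(1−q))
- Expected gain with no effect: (1−r)·λ
- Variance of T0 after exclusion: v = 1 − cλ − λ²
- SD of change: √[(1−r)²v + 1 − r²]
- Rejection: noncentral t, 152 df, noncentrality = gain / SD of change × √153, critical value 2.673

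**Worked case, q = 25%, r = 0.50.** c = 0.674, φ(c) = 0.318, λ = 0.318/0.75 = 0.424. Gain = 0.5 × 0.424 = 0.212 SD, or 3.2 points at SD 15 and 4.2 at SD 20. v = 1 − 0.286 − 0.180 = 0.535 (unrounded inputs). SD of change = √(0.25 × 0.535 + 0.75) = 0.940. Noncentrality = 0.212/0.940 × √153 = 2.79. Rejection probability: 55%.

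| Excluded | λ | Gain in SD (r = 0.75; 0.50) | Gain in points (SD 15–20) | Bonferroni T0–T3 contrast rejects |
|---|---|---|---|---|
| 10% | 0.195 | 0.049; 0.097 | 0.7–1.9 | 4–8% |
| 25% | 0.424 | 0.106; 0.212 | 1.6–4.2 | 23–55% |
| 40% | 0.644 | 0.161; 0.322 | 2.4–6.4 | 60–95% |

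The rejection rates do not depend on the assumed SD, which cancels. Their benchmark is the 0.8% level of a single adjusted contrast. They ignore the omnibus gate, which can only lower them. Simulation of the omnibus test itself under no effect (153 completers) gave rejection in 12–21% of studies at 10% excluded and 88–99.5% at 40%, against about 5% with no exclusion.

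**If the screen is not the T0 score** (simulated, 30% excluded)
- Screen error independent of T0: mean gain about 0, omnibus rejection about 5%.
- Error correlation 0.5: gain 0.06–0.12 SD, omnibus rejection 17–32%.

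**A separate screen taken at the same time.** Read together, an ICC of 0.75 and a between-visit correlation of 0.50 leave 0.75 − 0.50 = 0.25 of the variance as a passing state, which any concurrent screen shares with T0. For a screen of equal reliability with independent measurement error, excluding 25% gives 0.25 × 0.424 = 0.106 SD, or 1.6–2.1 points. Separateness alone is therefore not enough; timing matters too.

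**The case against.** The strongest reply is that the mechanism is conditional. No section says that the T0 SC-CII decides eligibility. Section 2.2 has eligibility verified from medical records by the referring clinician, and Section 2.14 has patients screened by nurses and enrolled after consent, which fits a screen made before the study questionnaires. If its error is independent of T0, the bias disappears. This stands: a reader might infer that the bias is certain, and the article does not support that. But nothing in the article secures the favourable case. Objective documentation is demanded only for diagnosis and clinical stability, self-report is allowed for behavioural variables, and Table 2 puts screening and baseline in one visit.

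Second, the size. A reader might infer a bias as large as the 8-point threshold. Under the assumptions used it stays below 8 in every case, and at 10% excluded it is under 2 points. The ICC is stated as a minimum; at r = 0.85 the range would be 0.4–1.9 points. Unadjusted T0–T3 tests at 5% would reject more often (14–24%, 48–79%, 83–99%), but that is not the planned contrast.

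Third, disclosure. The Abstract says that effectiveness is expected to be shown, not that it will be. The primary objective in the Introduction is only to quantify change. The missing control group is admitted and randomised designs are recommended for the future. The programme is openly described, so a reader who takes the non-interventional label as concealment goes too far; the sentence in Section 2.11 closes a paragraph on concomitant care. All this softens the charge. It does not name regression to the mean, and the sentence admitting the limit goes on to claim credible evidence from features that do not address it.

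**Conclusion.** The point holds as a gap in the plan, not as a demonstrated bias. Patients are selected low on the outcome construct at a visit not separated from the baseline measurement, and the uncontrolled change from that baseline is the primary endpoint. If the screen acts on the T0 score, the null gain is about 0.7–6.4 points. This would not by itself reach the 8-point threshold on average, but from about 25% excluded it makes a significant T0–T3 contrast weak evidence of any programme effect. These figures rest on the assumed exclusion share, SD, normality and selection on T0; the true size is unknown because the screen is undefined.

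Even with a clean screen, a single-group before–after comparison estimates within-participant change and cannot demonstrate effectiveness. The label in Section 2.1 and the last sentence on concomitant care in Section 2.11 conflict with a 12-month programme given to all participants. That is a separate inconsistency with no bearing on the size of the bias, but it needs to be reconciled.

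**What to change.** 1. **Section 2.2 and Table 2.** Base the self-care exclusion on information recorded before and separately from T0 (record review or a checklist by the referring nurse). State that the T0 SC-CII may not be used for eligibility, and take T0 only after eligibility is fixed.
2. **Strengths and Limitations.** Name regression to the mean as a limitation that the listed mitigations do not remove.
3. **Abstract and conclusions.** Replace the language of demonstrating effectiveness with estimating within-participant change, in line with the primary objective.
4. **Sections 2.1 and 2.11, and the registration.** Reconcile the non-interventional label and the statement on additional interventions with Sections 2.5 and 2.14, and describe a single-arm before–after study.

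Two remedies that may suggest themselves are better left out. A numerical correction using the observed correlation needs a cut-off on the T0 scale, which item 1 removes, and truncation attenuates that correlation (a true 0.50 becomes about 0.39 at 25% excluded). Using monitoring and management as untaught comparison domains at T1 fails because Section 2.4 says each session already includes techniques such as self-monitoring and problem solving.

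**Cost.** One eligibility rule, an ordering rule and some wording. Some patients with high T0 scores will enter, and the claim becomes more modest. According to Section 2.11, ethics approval was pending at submission and recruitment could not start before it. The rule should be in place before enrolment, because the selection cannot be undone afterwards.
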